#### Additional and subgroup analyses

Given the potential for participants to have more than one dengue infection during the study period, the rate of dengue infection will be modelled using Poisson regression, while using random effects strata, measurement period (baseline, first follow-up, second follow-up), household, and census tract (cluster). Additional baseline covariates may be considered for inclusion at the patient and household level (e.g., age, sex, socioeconomic status).

We will assess any differences in the associations of intervention and risk of dengue seroconversion by age group (≤ 5 yrs. and ≥ 6 yrs) and by socio-economic status (SES). Separately for the age group and SES variables, we will conduct a Cochran Q test [71] to test for differential changes in risk across time points between the vulnerable and non-vulnerable subgroups. Then, we will extend the models to allow for differential effects by including interaction terms between the intervention variable and a dummy variable for the vulnerable subgroup of interest [72]. We will finally consider an Oaxaca-Blinder decomposition analyses [73] to decompose the treatment effect variable between subgroups and estimate the exact contribution of the intervention to changes in inequities occurring after the implementation of the intervention. These are secondary objectives and the study may not be sufficiently powered to detect important differences between these subgroups for one or both variables.

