#### Outcomes

Primary outcomes are: rates of anti-dengue Immunoglobulin G (IgG) seroconversion (from negative to positive at follow-up) to evaluate the incidence of primary infections, and adult female *Aedes* density (number of adult female *Aedes* per household). Additional measurement of the antibodies waning rate or disappearance of detectable IgG antibodies (from positive at baseline to negative at follow-up), which may happen one to 2 years after primary dengue infections will determine the impact of the intervention on subsequent dengue secondary infections [48]. Secondary outcomes captured during household visits at baseline and follow-up are: i) anti-dengue IgG antibodies waning rates; ii) self-reported dengue during the most recent dengue season; iii) entomological indices: the container index (number of positive containers per household) and the premise condition index (how well the structure is maintain and yard), and, iv) knowledge, attitudes, and practices (KAP) for dengue control that will combined to create an index [49]. Secondary outcomes captured from the household survey, community focus groups, and in-depth individual interviews include: i) social acceptability of activities; ii) implementation fidelity and adaptability processes; iii) potential for sustainability, and iv) empowerment of individual and communities.

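### The Cochran Q step in the subgroup analysis does not test differential change between subgroups if it is the matched-samples test, and needs at-risk denominators and cluster-robust variance if it is the heterogeneity test

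*Protocol article*

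**What the plan says.** The section on additional and subgroup analyses in the protocol article looks for differences in the intervention's association with seroconversion "by age group (≤ 5 yrs. and ≥ 6 yrs) and by socio-economic status (SES"). Its first step, taken separately for each variable, is: "we will conduct a Cochran Q test [71] to test for differential changes in risk across time points between the vulnerable and non-vulnerable subgroups". The second step extends the multilevel models by "including interaction terms between the intervention variable and a dummy variable for the vulnerable subgroup of interest". A decomposition analysis comes third. The section closes with a caveat: "These are secondary objectives and the study may not be sufficiently powered to detect important differences between these subgroups".

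Three other statements bear on the first step.

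- The Outcomes section defines the outcome as "rates of anti-dengue Immunoglobulin G (IgG) seroconversion (from negative to positive at follow-up"), a measure of primary infection. It also expects some waning, "from positive at baseline to negative at follow-up), which may happen one to 2 years after primary dengue infections".
- The Statistical methods section gives the seroconversion model random effects for stratum, period, household and tract. It lists three periods, which leaves two intervals in which a child can convert.
- The Sample size section works with an ICC of 0.07 and 60 analysed children per cluster, and cites an ICC of 0.03 from the earlier community mobilization trial.

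The subgroup section does not say which Cochran Q is intended, how a child who has already converted is coded later, or what variance is used.

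**The concern.** The sentence ties a named test to a named hypothesis: that change over time differs between two groups of children. Two different tests carry this name. The reference to time points suggests the test for matched binary results in the same children. That test asks whether the proportion changes over time in one group. It says nothing about whether the change differs from that in another group. In its standard form it also takes children as independent, although they are sampled and randomized by tract.

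The interaction step does not fill the gap. It crosses intervention with subgroup and has no time term, so it addresses a different hypothesis. On the matched-samples reading, the equity analysis would open with a result that can be significant with no differential change and null when differential change is present.

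**Working it through.** **Inputs.** The article gives no figure for this test. Its sample-size inputs reproduce: 0.30 × (1 − 0.295) = 0.2115; 377.6 children per arm (unpooled formula, 80% power, two-sided 0.05); design effect 1 + 59 × 0.07 = 5.13; 377.6 × 5.13 / 60 = 32.3 clusters against 32 stated. ICC 0.07 and 60 per cluster are therefore used here as the plan's own values. Assumptions not in the article: risk per interval of 0.05 to 0.30, all children seronegative at the start, and even ages. On even ages the group aged 3 to 5 holds 3/7 of children: with 64 clusters of 60 (3,840), that is 1,646 against 2,194.

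**1. Matched Q and the stated hypothesis.** With two intervals Q reduces to McNemar's statistic, (b − c)² / (b + c), where b and c count children positive in only the first or only the second interval. The 5% critical value is 3.84. This step uses no clustering and no depletion.

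- Same fall, 0.20 to 0.12, in both subgroups: b − c = 0.08n and b + c = (0.2 × 0.88 + 0.8 × 0.12)n = 0.272n, so expected Q is about 0.0064n / 0.272. That is 38.7 for n = 1,646 and 51.6 for n = 2,194. Simulated rejection was about 100% in each, with no differential change.
- Opposite changes, 0.20 to 0.26 and 0.20 to 0.155: the net shifts are +0.06 × 1,646 = +98.8 and −0.045 × 2,194 = −98.7, which cancel. Pooled rejection was 5.6%, although the subgroups truly diverge.

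**2. Matched Q and clustering.** The smaller subgroup has about 60 × 3/7 = 25.7 children per tract. If tract risk varies independently between intervals, the variance of the change is inflated by 1 + 24.7 × ICC: 1.74 at ICC 0.03 and 2.73 at ICC 0.07. The type I error is P(|Z| > 1.96 / √inflation), which is 0.14 and 0.24. Simulation (1,000 runs per setting, risks 0.05 to 0.30, no depletion) gave:

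| ICC | Type I error |
|---|---|
| 0 | 0.05 to 0.06 |
| 0.03 | 0.14 to 0.15 |
| 0.07 | 0.21 to 0.26 |

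The inflation comes only from the part of tract risk that changes between intervals. With between-interval tract correlation r the factor becomes 1 + 24.7 × ICC × (1 − r) / (1 − ICC × r). At r = 0.7 it is 1.23 and 1.55, giving type I errors of 0.08 and 0.11. At r = 1 the inflation disappears.

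**3. Matched Q and children already converted.** Let risk be constant at h per interval, with n = 1,646 and ICC 0.

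- Converted children kept and coded 0 later: b = hn and c = h(1 − h)n, so the apparent fall is h².

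| h | Apparent proportions | Simulated false rejection |
|---|---|---|
| 0.05 | 0.050 to 0.048 | 0.05 |
| 0.10 | 0.10 to 0.09 | 0.16 |
| 0.20 | 0.20 to 0.16 | 0.76 |
| 0.30 | 0.30 to 0.21 | 1.00 |

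- Coded as cumulative status, or converted children dropped: b = 0 and c = h(1 − h)n, so Q = c. At h = 0.05 this is 78. Rejection was 100% at every risk tried, now as a false rise.

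**4. Heterogeneity Q.** Let d be the difference between subgroups in log(risk in interval 2 / risk in interval 1). Then Q = d² / Var(d). The simulation (600 runs) used constant risks of 0.25 and 0.15 and a tract-by-interval multiplier with mean 1 and variance 0.3. The implied ICC is 0.3p / (1 − p), or 0.10 at p = 0.25 and 0.053 at p = 0.15.

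| Denominator and variance | Subgroup varies within tracts | Subgroup follows tracts |
|---|---|---|
| At-risk, naive | 0.053 | 0.333 |
| At-risk, cluster jackknife | 0.053 | 0.055 |
| Full cohort, naive | 0.23 | 0.46 |

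The full-cohort denominator fails because depletion alone shifts the log ratio by ln 0.75 = −0.288 in one subgroup and ln 0.85 = −0.163 in the other. That is a false differential change of −0.125.

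**The case against.** The strongest reply is that the variant is open. The cited reference is not part of the article, and a comparison between two subgroups also describes the heterogeneity Q. That test can compare subgroup-specific changes and holds its level when built properly. For a variable that differs within tracts, as age does, even naive variance with at-risk denominators gave 0.053. This stands, so a reader should not infer that any Cochran Q is incapable of the comparison.

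Three further inferences are tempting and go beyond the text.

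- **A certain false fall in risk.** The sign depends on a coding that the article does not state, and the fall is negligible at 5% risk per interval. The article's allowance for waning also means that a second conversion is possible in principle, although the first can happen only once.
- **A decision to ignore clustering.** The standard matched test ignores it, but the article does not say that clustering will be left out, and the models extended in the next step carry tract random effects.
- **Loss of incompletely followed children.** The Missing data section plans multiple imputation of the serological outcome and inverse probability of censoring weights.

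It is also fair that the interaction step, which does not depend on the Q result, serves the section's opening aim of comparing intervention effects between subgroups. It does not serve the Q sentence, which concerns change over time. Coding and variance details may sit in a fuller document, but the pairing of test and hypothesis is fixed in the article.

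**Conclusion.** The point holds in conditional form. If the matched-samples Q is meant, it does not test the stated hypothesis. That conclusion needs no assumption about ICC or coding. Its over-rejection under clustering (0.14 to 0.15 at ICC 0.03, 0.21 to 0.26 at ICC 0.07) assumes tract risk that varies independently between intervals, and shrinks as tract risk becomes more stable. The distortion from converted children depends on coding and on the risk per interval. If the heterogeneity Q is meant, the comparison is possible. It still needs at-risk denominators and cluster-robust variance, above all for SES if SES follows the tract; how closely it does is not stated, and 0.333 is the fully tract-level case.

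A reader might conclude that the trial's main result is compromised. It is not: this is a secondary analysis that the article itself says may lack power, and the primary analysis and sample size do not depend on it.

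**What to change.** Replace the Cochran Q step with a subgroup-by-period term in the planned clustered model for seroconversion. Restrict each interval to children seronegative at its start. Enter period and the lower-order terms as fixed effects, because period is currently a random effect. If change over time in the intervention effect is also of interest, add intervention by subgroup by period as a separate question, and expect less power for it.

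Alternatively, keep the name but state that the heterogeneity Q is applied to subgroup-specific changes, with at-risk denominators and cluster-robust variances (for example a jackknife over tracts) that allow for both subgroups sharing tracts.

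Either route costs a little more model specification. No data collection, sample size or primary analysis changes.

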### Trial design

We will follow a parallel pragmatic cluster randomized controlled trial (cRCT) design with randomization at the census tract level with equal allocation to the two arms, to evaluate the effectiveness of community mobilization measured by the risk of primary DENV infection, self-reported dengue cases, and *Aedes* infestation rates. The quantitative baseline assessment will include a household questionnaire, entomological evaluation of households and high-risk communal areas, and blood samples (from finger pricks) from children aged 3–9 years. Following the baseline assessment, allocation will occur after which community mobilization activities will begin for a period of 24 months. Baseline community interviews and focus groups for the qualitative studies will be performed just after allocation.

This is an investigator-initiated trial that was registered with ISRCTN66131315 prior to enrollment. The trial protocol was developed according to the Standardized Protocol Items: Recommendations for Interventional Trials (SPIRIT) guidelines (Additional file 1) [35].

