#### Contamination

Despite the protective measure of excluding clusters that are within 800 m from another cluster, there will likely be contamination through people interacting between the clusters at the individual or household level and through schools [8]. In addition, mosquitos from neighbouring households may influence rates in the intervention sites and children may get bitten by infected mosquitos outside of their intervention site. Both types of contamination will reduce the measured difference between control and intervention clusters although we will document the spread of intervention beyond the intervention clusters by monitoring any changes in behaviors within households and at the cluster level. Furthermore, we will collect school data from participating children including GPS coordinates for the schools and identify if the school is in a control or treatment area. This information will be included in the final analysis to estimate the impact of potential contamination on our findings.

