### Statistical methods

We will follow an intention-to-treat (ITT) approach. To estimate the potential impact of the intervention on the risk of dengue seroconversion, we propose a conditional (multilevel) modeling approach (i.e., using mixed effects models) [69]. To estimate the incidence risk ratio of seroconversion in the intervention group relative to the control group, a log-binomial model will be used which assumes a log link under the assumption of a binomial distribution [70]. Since the intervention effect of marginal and conditional models are only the same for the identity and log links [69], if convergence is an issue, a robust Poisson model with log link and robust variance will be used [70]. In addition to the fixed effect for the intervention, the log-binomial mixed model will have random effects for strata, measurement period (baseline, first follow-up, second follow-up), household, and census tract (cluster). The random effects for period will allow us to assess period by period differences in the risk of seroconversion. Also, as an alternative to the strata random effects, we will consider the baseline risk indicator (cumulative dengue incidence at the bairro level) that was used to stratify clusters. Additional baseline covariates may be considered for inclusion at the patient and household level (e.g., age, sex, socioeconomic status). We anticipate that the cluster sizes will remain relatively similar across all clusters but if losses due to attrition result in significant differences, we will then use inverse probability weights by cluster size in the analysis. For the primary outcomes of adult female *Aedes* density, we will use the same approach: a conditional (multilevel) modeling approach (i.e., using mixed effects models) with a Poisson distribution. For KAP and social capital, they will be examined as potential effect modifiers/confounders with each outcome. An index of KAP will be created using principal component analysis. Additionally, indicators on the community interventions captured from the fidelity analysis (e.g., content, coverage, frequency, and duration) may be included as fixed effects in the models to estimate the impact of intervention variability on the results.

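### The age and SES interaction tests name no tract-by-subgroup variance, so they are anti-conservative if the subgroup gap differs between tracts

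*Protocol article*

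**What the plan says.** Under Trial design, the protocol article specifies "randomization at the census tract level with equal allocation to the two arms".

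Under Statistical methods, the seroconversion model is set out with its random part: "the log-binomial mixed model will have random effects for strata, measurement period (baseline, first follow-up, second follow-up), household, and census tract (cluster". The same section has one fallback: "if convergence is an issue, a robust Poisson model with log link and robust variance will be used". It does not say at which level that robust variance is clustered.

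Under Additional and subgroup analyses, the same four random effects are listed again for the infection-rate model. Differences in effect are then examined by age (5 years and under against 6 years and over) and by SES, for which no cut-off is given. The step that tests for a differential effect is to "extend the models to allow for differential effects by including interaction terms between the intervention variable and a dummy variable" for the vulnerable subgroup. No change to the random part accompanies it. The section closes with a caveat: "These are secondary objectives and the study may not be sufficiently powered to detect important differences between these subgroups".

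**The concern.** An arm-by-subgroup interaction in a cluster trial is a difference of differences. Within each tract there is a gap between vulnerable and non-vulnerable children, and the interaction asks whether the average gap differs between intervention and control tracts. The independent units for that comparison are the tracts, so the error must include how much the true gap varies from tract to tract.

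None of the listed effects supplies that variance. Tract, stratum and period effects shift both subgroups together and cancel from the gap. Household effects are independent between households, so they cannot represent a gap shared across a tract.

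The protocol gives some reason to think that the gap could vary. The Contamination section expects that "children may get bitten by infected mosquitos outside of their intervention site" and mentions mixing through schools, which could matter differently at ages 3 to 5 and 6 to 9. The Intervention section lets each intervention cluster design its own activities (school visits, clean-ups, text messages), and these could reach subgroups unevenly from one tract to the next.

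At stake is a chance subgroup difference reported as differential benefit by age or SES. That would feed the objective on heterogeneity of effect and the planned decomposition of changes in inequities.

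**Working it through.** **The plan's own figure.** The inputs under Sample size are control risk 0.30, intervention risk 0.2115, ICC 0.07, 60 children per tract, 80% power and a significance level of 0.05 (taken as two-sided). The design effect is 1 + 59 × 0.07 = 5.13. The unpooled two-proportion formula gives 377.6 per arm before clustering, and 377.6 × 5.13 / 60 = 32.3 tracts, against the stated 32. Two spare tracts make 34 per arm. The main-effect calculation therefore reproduces; the plan states no figure for the interaction.

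**Inputs for the interaction.**
- From the protocol: 34 tracts per arm, m = 60 analysed children per tract, p = 0.30, ICC 0.07, and ICC 0.03 (reported in the same section for children aged 3 to 9 in the earlier trial across 150 clusters).
- Assumed: equal numbers per year of age, so a 3:4 split (25.7 and 34.3 children per tract).
- Assumed: ρ, the correlation between the two subgroups' tract effects, from 1 to 0.7. The protocol gives nothing from which to estimate it.

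**Formulas, per tract.**
- Variance of the true gap between tracts: G = 2 × ICC × p(1−p) × (1−ρ)
- Sampling variance within a tract: W = p(1−p)(1−ICC)(1/m₁ + 1/m₂)
- The model without a tract-by-subgroup term keeps only W. The ratio of true to assumed variance is R = 1 + G/W, and p(1−p) cancels.
- False-positive rate at nominal 5% = 2[1 − Φ(1.96/√R)]

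**Worked case, ICC 0.07, ρ = 0.8.** G = 2 × 0.07 × 0.21 × 0.2 = 0.00588. W = 0.21 × 0.93 × 0.06806 = 0.01329. R = 1.442, √R = 1.201, 1.96/1.201 = 1.632, and the false-positive rate is 10.3%.

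**Analytic results (nominal 5%).**

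| ρ | ICC 0.07, m = 60 | ICC 0.03, m = 60 | ICC 0.07, m = 30 | ICC 0.03, m = 30 |
|---|---|---|---|---|
| 1 | 5.0% | 5.0% | 5.0% | 5.0% |
| 0.9 | 7.6% | 6.1% | 6.3% | 5.5% |
| 0.8 | 10.3% | 7.1% | 7.6% | 6.1% |
| 0.7 | 12.9% | 8.2% | 8.9% | 6.6% |

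The m = 30 columns are an illustration. The outcome is conversion from negative to positive, so only seronegative children contribute, and fewer of them means a larger W and less inflation. A 50:50 split, as might apply to SES, gives 7.7%, 10.4% and 13.0% at ρ = 0.9, 0.8 and 0.7 (ICC 0.07, m = 60).

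**Simulation.** Binary data on the log-risk scale, 34 tracts per arm, ICC 0.07, m = 60, no true interaction, 10,000 runs per setting. The rates were 5.1%, 7.0%, 9.1% and 11.7% at ρ = 1, 0.9, 0.8 and 0.7. On the same data, tract-clustered robust variance and a t-test on the 68 tract gaps both stayed between 4.7% and 5.3% for every ρ from 1 to 0.5. The simulated test used a within-tract contrast in place of the full log-binomial mixed model, so the figures are approximate.

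**The case against.** The strongest reply is that this reads too much into a condensed article. The text never uses the word intercept and never excludes random slopes, and covariance structure is often settled in the SAP. That is partly fair. A reader might infer that the plan commits to a tract intercept and nothing else, and the documents do not say so. But the article does state both the random effects and the extension, and what it states has no term for a tract-varying gap.

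A reader might also infer that false subgroup findings will be too frequent. The documents do not support that as a fact. It depends on ρ, which is assumed; at ρ = 1 the test keeps its level, and at ICC 0.03 the inflation is small. That differential exposure varies by age and tract is plausible, but the protocol does not assert it. The Contamination section also plans to record each child's school and its study area and to use this in the final analysis, which would absorb part of that mechanism.

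The robust Poisson fallback would protect the test if clustered by tract. It applies only on non-convergence and its level is unstated, so it cannot be relied on.

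SES is probably a household rather than a child characteristic. The argument still applies to the extent that it varies within tracts.

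Finally, the analyses are declared secondary and possibly underpowered. That limits the weight of the point, but the caveat warns of missed differences, not of spurious ones.

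**Conclusion.** The point holds in conditional form and is minor. As listed, the subgroup models allow nothing for tract-to-tract variation in the age or SES gap, and if that variation exists, the interaction standard errors are too small. Over the assumed range of ρ from 1 to 0.7, the nominal 5% test runs at about 5% to 13% with ICC 0.07 and 60 children per tract, and about 5% to 8% with ICC 0.03. Both ranges shrink as the number of at-risk children falls. The lower end is no problem at all, and nothing in the protocol says where in the range the trial will lie. The concern is confined to the secondary interaction tests. It gives no reason to doubt the main intervention estimate or the sample size. Exploration of heterogeneity does not rest on these tests alone, since fidelity indicators, spatial analyses and realist evaluation also address it.

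**What to change.** In Additional and subgroup analyses, or in the SAP, state how the error of the age and SES interaction tests is obtained. Any of these would do:
- robust variance clustered by census tract;
- a comparison between arms of the tract-level subgroup gaps;
- a tract-by-subgroup random effect (a random slope of the vulnerable dummy by tract), with one of the first two as the named alternative if the model does not converge.

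If the Poisson fallback is kept, say that its robust variance is clustered by tract.

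The cost is a sentence in the plan and somewhat wider intervals for these secondary tests. The random-slope model is harder to fit, and the tract-level comparison needs children of both subgroups in each tract used. When the gap does not vary between tracts, the two tract-level methods still held close to 5% in the simulation, so false-positive control is not lost by adopting them.
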